## Abstract

**Background/Aim**: We have a limited understanding of the broader determinants of health of international migrants and how these change over time since migration to the United Kingdom (UK). To address this knowledge gap, we aim to conduct a prospective cohort study with data acquisition via a smartphone application (app). In this pilot study, we aim to 1) determine the feasibility of the use of an app for data collection in international migrants, 2) optimise app engagement by quantifying the impact of specific design features on the completion rates of survey questionnaires and on study retention, 3) gather preliminary profile health status data, to begin to examine how risk factors for health are distributed among migrants.

**Methods**: We will recruit 275 participants through a social media campaign and through third sector organisations that work with or support migrants in the UK. Following consent and registration, data will be collected via surveys. To optimise app engagement and study retention, we will quantify the impact of specific design features (i.e. the frequency of survey requests, the time of day for app notifications, the frequency of notifications, and the wording of notifications) via micro-randomised process evaluations. The primary outcome for this study is survey completion rates with numerator as the number of surveys completed and denominator as the total number of available surveys. Secondary outcomes are study retention rates and ratings of interest after app usage.

**Ethics and dissemination**: We have obtained approval to use consented patient identifiable data from the University College London Ethics Committee. Improving engagement with the app and gathering preliminary health profile data will help us identify accessibility and usability issues and other barriers to app and study engagement prior to moving to a larger study.

## Introduction

During their journey and after arrival in their host country, migrants experience large, rapid changes in the wider determinants influencing their health, including different legal, social, economic and health structures and systems; health service access and support; exposures and behaviours; and epidemiological changes associated with population mobility (
Figure 1)
^1^. In the UK there is a limited understanding of how these factors are distributed among migrants and how they change over time since migration. 

**Figure 1. f1:**
[figure not shown]
A conceptual framework for influences on migration and health adapted from UCL-Lancet Commission on Migration and Health
^1^. Boxes in green may apply at the individual, population or system level or a combination. The green boxes in the centre delineate four fundamental factors that influence the interactions between health and mobility. At the top, Structures and Systems, indicate the role of policies and legislation (e.g. immigration laws, human rights standards, entitlement schemes), the health system (e.g. design, funding, quality), socio-cultural factors (e.g. integration policies) and economic structures (e.g. employment access, financial protections). The second box, Access to Services and Support, refers to how migrants access and use health and non-health services and social services in their place of origin versus a destination location. Migrant Health Influences suggest the multiple exposures and behaviours that will influence migrants’ safety, health and wellbeing. The bottom box highlights Epidemiological Changes, expressing the rapid shifts that can occur at a population level, which may affect global, regional, national or specific population prevalence and incidence of communicable and non-communicable diseases and injuries. Grey arrows represent the migration-related health influences from the place of origin. The purple arrows represent migration or migrant-related health influences that emerge, decrease or increase at a transit stage and/or in the destination. Finally, the return arrow explicitly recognises the fact that many migrants will not remain in their destination country - the timing of which can vary considerably.

Gathering information about the health of migrants — which depends on the interaction between people, health systems and wider society — is challenging because migrant populations tend to be fluid in terms of mobility
^1^. Someone who has migrated recently may change address many times before settling. While many people migrate to the UK to rejoin their families, some migrants may initially not live in established households and may temporarily reside in short-term lets, hotels, hostels, shelters, caravan parks and other communal establishments.

One potential solution to improve data collection for research studies in mobile populations is to enable data collection via a smartphone application (app). Apps may have a particular use with mobile populations, such as migrants, with evidence suggesting that even the most excluded migrant populations have high levels (80–90%) of smartphone possession
^2^. During their migration journey, migrants use smartphones to communicate and access the internet, often using multiple sim cards, avatars and pseudonyms
^3^.

Smartphones are carried by migrants within the UK after arrival, thus they can inform us of their health needs and health determinants remotely — and continuously. An app that collects data can remove many barriers associated with conventional research studies, but we do not currently have good evidence on the acceptability of or engagement levels with research apps in migrant populations. Studies have been conducted in the general population that examine the barriers to and facilitators of engagement
^4^ and indicators of retention
^5^, with few studies specifically focused on the impact of survey content, schedules, and app notifications (frequency, timing and content) on engagement with mobile app research. Moreover, we have not found any studies conducted in migrant groups on engagement with research apps. We have designed an app for quantitative data collection in the UK migrant population, the Health On the MovE (HOME) app. Prior to running a large prospective longitudinal cohort study using the HOME app, we are conducting a pilot study — which this protocol describes — in order to test the feasibility of conducting research using an app in this study population and to fill the knowledge gap on how best to optimise engagement with app research in migrants.

## Aim and objectives

This study aims to pilot (or beta-test) the HOME app-enabled data collection platform to examine the health and wellbeing of migrants in the UK.

There are three main objectives of this pilot study:

1) To determine the feasibility of the use of the app for data collection in recent/long-term international migrants residing in the UK.2) To optimise engagement in the study by quantifying the impact of specific app design features on completion of survey questionnaires and study retention.3) To gather preliminary profile health status data, to begin to examine how risk factors for health and wellbeing are distributed among migrants and how they vary over time since their migration to the UK.

## Protocol

### Study design

This will be a longitudinal study with embedded micro-randomised process evaluations with each participant followed up for three months.

### Study recruitment

We will conduct a social media recruitment campaign working with partners in the UK that have an active online presence and work with migrants. An animated promotion video (
https://youtu.be/r314pjzxmn8) was made to maximise the recruitment potential and help explain the study and its aims. Participants may also be approached through third-sector organisations that work with or support migrants in the UK who we will work with to distribute information to potential participants — either via email or using printed study materials.

Once the study is launched, any eligible individual will be able to download the HOME app on Apple app or Google Play stores. Explicit consent will be obtained as part of the study registration process on the app.

### Eligibility criteria

To be eligible for the study, individuals need to be at least 18 years old, born outside of the United Kingdom and currently living in the UK. With this, we aim to reach migrants who are UK residents and are settled or are in the process of settling here.

For this study protocol, we define migrants as people born outside of the UK that are currently residing in the UK, regardless of the characteristics of migration (eg. when it occurred, at what point during their lifetime, and for how long), their reason to migrate and their migration status. This includes people who either have chosen to migrate (e.g. to work, study, or join families) or those who may have been forced to migrate due to conflict, persecution or environmental disasters (e.g. refugees and asylum seekers).

### Consent

Before consenting to participate, individuals are given in-app information on time commitment, benefits and disadvantages to participation, data collection, privacy and data protection, modes of dissemination of study findings and follow-up, and on how to contact the team or to withdraw from the study. Explicit consent is sought for the collection of data about physical, mental, and sexual health. 

### Registration

Directly following the consent process and registration, participants will be asked to complete a baseline demographics survey.

### Data collection

Personal data will be collected using the app, that will have been downloaded onto the participants’ smartphone. Personal data collected will include demographic information, such as name (first and surname), email, sex, date of birth, country of origin, ethnicity, and visa category. The participant will then be asked — once or twice weekly — to complete a short health status survey, lasting between 15 to 60 seconds (see
*Extended data* File 1)
^6^. In addition to these short surveys, once a week, participants will be asked to fill in one of the 13 surveys that cover health, social, work or lifestyle-related topics (5-minute surveys; see
*Extended data* File 1)
^6^. The topics of these surveys have been previously identified as knowledge gap areas by the UCL-Lancet Commission on Migration and Health and after discussions with migrants and relevant thematic experts following focus group sessions. All of the 13 surveys to be administered are validated surveys, or have taken questions from a validated survey and adapted them for the population and the app. Participation in the pilot study will last a total of 12 weeks. Migrants will be asked to complete weekly surveys via notifications from the HOME app.

### Participant engagement and retention

Micro-randomised process evaluations (MRPE) will be used to optimise participant engagement and retention in the final design of the study (see below). Structured feedback on engagement will be obtained through a short, interest-focused survey, administered once per week within the app. In a separate focus group study, we will seek feedback from migrants on barriers and enablers to engagement with the app. Participants who complete less than 20% of surveys during the three months of the study, will be followed up via email to ask about reasons for discontinuation to examine issues of acceptability.

Participant engagement and retention will be fostered by sending out communications via email and on our website every few weeks containing general findings throughout the course of the study. These regular communications were added as a direct result of feedback from focus groups — run to inform the design of the study — in which participants expressed the desire for regular updates about the study's findings. We will also continue to engage and promote the study throughout.

### MRPE

In order to increase survey completion rates and reduce selection bias (via a loss to follow up), we will conduct a series of micro-randomised process evaluations that are designed to address evidence gaps that we identified prior to starting the study
^4^ and after feedback from our focus group participants:

1. Schedule of short surveys — twice weekly (e.g. day 3 and 7) vs. weekly (e.g. day 7).2. Timing of initial survey notification — which appears the next day if the survey has not yet been completed — 16.00 vs. 21.003. Timing of survey notification reminders: reminders to be sent to those not having completed a survey 1 day vs. 3 days after initial notification of the survey.4. Text content of initial survey notifications: Two versions of notification text to be drafted — one using conventional wording and a second that is informed by Barriers to and Facilitators of Engagement With Remote Measurement Technology
^4^ and the COM-B model
^7^.5. Text content of reminder survey notifications: Two versions of notification text to be drafted — one using conventional wording and a second that is informed by Barriers to and Facilitators of Engagement With Remote Measurement Technology
^4^ and the COM-B model
^7^.

Figure 2 outlines how micro-evaluations will be conducted sequentially and illustrates how evaluation 2 (Timing of survey notification reminders) will only begin once we have statistical power to answer evaluation 1 (Schedule of short surveys — twice-weekly vs. weekly) in terms of survey completion rates.

**Figure 2. f2:**
[figure not shown]
Flow diagram of study plan of micro-randomised process evaluation studies. *default schedule at baseline e.g. prior to running the test on. Survey schedule A is twice-weekly short surveys and schedule B is once-weekly short surveys.

### Primary outcomes

The primary outcome for this study is survey completion rates with numerator as the number of surveys completed and denominator as the total number of available surveys.

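### The primary completion rate pools 15–60 second and 5-minute surveys in one unweighted ratio, so it cannot show topic-survey completion and it shifts with the survey schedule

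*Protocol article*

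**What the plan says.** Under Primary outcomes, and in the same terms in the Abstract, the protocol article sets a single ratio with "numerator as the number of surveys completed and denominator as the total number of available surveys". It does not split, weight or restrict the ratio by type of survey.

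Data collection describes what is available to be completed. Once or twice weekly, participants are asked "to complete a short health status survey, lasting between 15 to 60 seconds". Once a week, "participants will be asked to fill in one of the 13 surveys that cover health, social, work or lifestyle-related topics"; these are labelled as 5-minute surveys. "Participation in the pilot study will last a total of 12 weeks".

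A third instrument appears under Participant engagement and retention: "Structured feedback on engagement will be obtained through a short, interest-focused survey, administered once per week within the app". The article does not say whether it counts in the ratio.

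The MRPE section makes the short-survey schedule (twice weekly against weekly) the first randomised comparison and says that it is answered in terms of survey completion rates. The first secondary outcome, the proportion of participants completing more than 80% of surveys, uses the same undivided count. The Analysis plan assumes one baseline completion of 20%, without reference to survey type.

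**The concern.** A topic survey takes 5 to 20 times as long as a short one (300 seconds against 60 or 15), yet each adds one to the numerator and one to the denominator. Two consequences follow.

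First, the primary figure is a mixture of two rates. The pilot is meant to establish whether the app can collect the study's data, and the social, work and lifestyle content sits in the topic surveys. A mixture can look acceptable while one component is poor, and a reader given only the mixture cannot tell which.

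Second, the mixing weights are not constant. They depend on the short-survey schedule, which evaluation 1 deliberately varies. A rate whose denominator changes composition between randomised arms can differ between them for reasons unrelated to engagement.

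**Working it through.** The plan states no figure for completion by survey type, so there is nothing to reproduce. The check is how the ratio behaves as written.

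**Inputs from the article.** Short surveys: 1 or 2 per week. Topic surveys: 1 per week. Interest survey: 1 per week, status in the ratio unstated. Follow-up: 12 weeks. Planning completion: 20%. Completion by type is not given, so the pairs used below are assumptions.

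**Step 1: share of short surveys in the denominator, w.**
- Weekly: 12 / (12 + 12) = 50%.
- Twice weekly: 24 / (24 + 12) = 67%.
- If the interest survey counts as a further brief survey: (12 + 12) / 36 = 67% and (24 + 12) / 48 = 75%.
- If all 13 topics were offered instead of 12: 12 / 25 = 48% and 24 / 37 = 65%.

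**Step 2: pooled rate.** Pooled = w × short rate + (1 − w) × topic rate. Interest surveys are left out here.

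| Assumed short / topic | Pooled, weekly | Pooled, twice weekly | Pooled minus topic (weekly; twice weekly) | Twice weekly minus weekly |
|---|---|---|---|---|
| 20% / 20% | 20.0% | 20.0% | 0; 0 points | 0 points |
| 25% / 15% | 20.0% | 21.7% | +5.0; +6.7 | +1.7 |
| 30% / 10% | 20.0% | 23.3% | +10.0; +13.3 | +3.3 |
| 40% / 10% | 25.0% | 30.0% | +15.0; +20.0 | +5.0 |
| 10% / 30% | 20.0% | 16.7% | −10.0; −13.3 | −3.3 |

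For example, 30% / 10% on the twice-weekly schedule is (24 × 0.30 + 12 × 0.10) / 36 = 8.4 / 36 = 23.3%.

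**Step 3: how little the pooled figure constrains topic completion.** A pooled 20%, the plan's own planning value, is reached with no topic survey completed if short completion is 0.20 / 0.50 = 40% (weekly) or 0.20 / 0.667 = 30% (twice weekly). A participant who completes every short survey passes the 80% secondary outcome with 8 of 12 topic surveys on the weekly schedule (20 / 24 = 83.3%) and with 5 of 12 on the twice-weekly schedule (29 / 36 = 80.6%).

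**Step 4: evaluation 1.** Hold the type-specific rates identical in both arms. The difference in pooled rate is then (2/3 − 1/2) × (short − topic) = (short − topic) / 6. At 40% and 10% this is 0.30 / 6 = 5.0 points: 25.0% weekly against 30.0% twice weekly. The weekly mix is 1:1 or 2:1 however long the evaluation runs, so the gap does not depend on its duration. Five points is also the smallest difference that the Analysis plan considers (20% against 15%).

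**The case against.** Several stronger readings are tempting, and the documents do not support them.

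- **That the short surveys drive the primary figure.** This is so only on the twice-weekly schedule, or if the interest survey counts. On the weekly schedule the two types weigh equally, and evaluation 1 may select that schedule.
- **That the pooled rate overstates topic completion.** This needs short surveys to be completed more often. Their length makes that plausible, but the article does not say it. Equal rates give no bias, and the opposite pattern reverses the sign.
- **That the topic rate is the one feasibility figure that matters.** Objective 1 concerns data collection by app in general. Objective 3 begins with health status data, which the short survey collects, and the Discussion relies on continuous measurement of changes in mental and physical health. Both instruments supply data that the cohort needs.
- **That the larger study would be sized on the wrong number.** The article does not say that this rate will size the larger study and sets no feasibility threshold on it. It says only that the pilot will inform that study's conduct.

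A further objection is that a breakdown by instrument is reporting detail for a statistical analysis plan that is not shown. A table by type may indeed be planned there. But the article does fix the primary outcome, and fixes it as one ratio over all available surveys. A supplementary table elsewhere would not change what that ratio measures.

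On evaluation 1, the Analysis plan's example speaks of the percentage of migrants completing a questionnaire, so the quantity used in the decision rule may not be the pooled ratio. That part of the point is therefore conditional.

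**Conclusion.** The point stands in a limited form. As defined, the primary outcome mixes two instruments of very different burden and cannot show whether the topic data are obtainable. Its value also depends on the schedule, because the short share of the denominator moves from 50% to 67%. These statements follow from the article's own counts and need no assumption about completion.

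The size and direction of any distortion do rest on assumed rates. Over the pairs examined, the pooled rate lies from 13 points below to 20 points above the topic rate, and is unbiased when the two rates are equal. If evaluation 1 is judged on the pooled ratio, the artificial gap between arms is one sixth of the difference between the short and topic rates: 5 points at an assumed 40% and 10%.

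**What to change.** - Define and report the primary completion rate separately for the short health status surveys and the 5-minute topic surveys. Compute each as a per-participant rate (that participant's completed over available surveys of the type) and then summarise across participants.
- Keep the pooled ratio as a descriptive summary.
- State whether the weekly interest survey and the baseline demographics survey count in any of these rates.
- Compare the evaluation 1 arms on type-specific rates, and say which of them enters the expected-loss decision rule.
- Carry both rates forward to inform the larger study.

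This uses data that the app already collects. The cost is a change of wording, one extra table and a headline figure that may be lower than the pooled one. The sponsor must also choose explicitly which rate governs evaluation 1.

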### Secondary outcomes

1) Proportion of participants completing greater than 80% of surveys during the three months of the study.2) Weekly ratings of “Interest” after app usage. The affective state of “Interest” has previously been identified as a significant predictor of participant engagement with mobile apps
^8^.

### Participant timeline

Figure 3 illustrates a series of typical participant timeline interactions with the HOME app timelines under different scenarios, including twice-weekly short survey schedules with reminders required and weekly short surveys with no reminders required.

**Figure 3. f3:**
[figure not shown]
Participant timeline.

### Assignment of interventions

***Allocation.*** Participants will be allocated to the different micro-evaluations using the A/B testing feature on Google Firebase which uses computer-generated random numbers. These allocations will occur during the recruitment and then again after the completion of each MRPE. Participants and the study analyst will be blinded to the allocation.

### Data management and analysis

***Data flow and management.*** Data flows and data management are described in detail in
*Extended data* File 2
^6^, including those for participant registration, survey notification, survey data collection, and data extraction. All data will be securely transferred by HTTPS and stored on secure servers through Amazon Web Services (AWS) and the UCL Data Safe Haven.

***Bias.*** To minimise measurement bias, we have used survey questionnaires previously validated wherever possible. The series of micro-randomised process evaluations we are undertaking aim to reduce bias in the main study by increasing engagement and reducing loss to follow up in the study. 

***Analysis plan.*** For the HOME app, there are five different aspects of the app which we wish to assess sequentially, in terms of their effects on response rates.
Table 1 lists these five aspects, in the order planned for assessment. In each case, the response rate (baseline completion) is assumed to be 20%. For each modification, we have assumed an optimistic difference (the extent to which we hope the new version will increase response rates), and a pessimistic difference (the extent to which the new version may decrease response rates). For example, for the survey schedule, we expect 20% of migrants to complete the questionnaire using the standard version of the app. We hope that 40% of migrants who get more frequent notifications will complete the survey. However, if participants find the notifications intrusive it may be that only 5% of migrants will complete the questionnaire under the more frequent notifications condition.

**Table 1. T1:** Parameters for power calculations for the migrant app.

	Assumed completion rates under the two options			Approximate probability of choosing better option under proposed design	
Test	Baseline completion	Optimistic difference	Pessimistic difference	Optimistic difference	Pessimistic difference
Survey schedule	20	20	5	90%	65%
Time of initial notification	20	20	5	90%	65%
Time of reminder notification	20	20	5	90%	65%
Text content of initial notification	20	10	5	75%	65%
Text content of reminder notification	20	10	5	75%	65%

Rather than power the study for traditional hypothesis tests for these 5 aspects relating to optimising the app, for each aspect we will apply a decision rule which chooses the option which leads to an expected loss in subsequent responses which is less than a pre-specified threshold of acceptable loss. This decision will be made as soon as sufficient information is available to make that decision. Additionally, a pre-specified maximum number of participants (per aspect) will be defined. Once this is reached, the option leading to the lowest expected loss (whether this is under the threshold or not) will be chosen.

Due to a lack of closed-form power calculations for this approach, the simulation was used to decide (i) the initial number of participants required prior to first calculating the expected loss under each option, (ii) the maximum participants per aspect. Using a threshold of 1% for an acceptable subsequent loss in responses, simulation studies showed that taking an initial group of 10 participants, updating the decision rule as data accumulates, and making a decision with a maximum of 50 participants per aspect, gives a high probability of choosing the correct option (analogous to the power) for each aspect (
Table 1). The lowest probability occurs if the completion rate is 20% under one option and 15% under the other, in which case the proposed design gives approximately 65% of choosing the better option. For slightly bigger effects (e.g. 20% completion under one option and 30% under the other), then the probability of choosing the better option is higher (75%).

In the first phase, we will summarise and compare baseline characteristics between the migrant group and the general population in the UK. We will review levels of missing data, but we anticipate that these will be analysed grouped as “not recorded”. We will analyse each MRPE after it has been delivered to 50 participants. 

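### Re-allocated participants bring a stored completion history into evaluations 2 to 5, but the decision rule is built on two completion rates alone: a modest, cheap gain in precision goes unused

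*Protocol article*

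**What the plan says.** All references are to the protocol article.

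- *Data management and analysis, Analysis plan*: "there are five different aspects of the app which we wish to assess sequentially, in terms of their effects on response rates". There is to be no conventional test: "Rather than power the study for traditional hypothesis tests for these 5 aspects", the rule "chooses the option which leads to an expected loss in subsequent responses which is less than a pre-specified threshold of acceptable loss". The operating settings are "Using a threshold of 1% for an acceptable subsequent loss in responses" for the threshold, "taking an initial group of 10 participants, updating the decision rule as data accumulates" for the looks, and "making a decision with a maximum of 50 participants per aspect" for the ceiling.
- *Table 1* gives the approximate probability of choosing the better option as 90% (20% v 40%), 75% (20% v 30%) and 65% (20% v 15%). Each scenario is defined by two completion rates and nothing else.
- *Assignment of interventions, Allocation*: "These allocations will occur during the recruitment and then again after the completion of each MRPE".
- *Primary outcomes* defines completion as surveys completed over surveys available. *Data collection* asks for a short survey once or twice a week and a topical survey once a week, over 12 weeks.

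No part of the article mentions earlier completion as a covariate or a stratification factor.

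**The concern.** A person re-allocated after an earlier evaluation already has a completion rate in the app. That rate is a baseline value of the outcome itself. Because it precedes the new allocation, it can be adjusted for safely, even though it was partly gathered under a different setting of the app. It is plausibly the best available predictor of whether the person answers the next survey.

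Each choice rests on at most 50 people in total. In such small groups one option can do better partly because it drew more habitual responders. The weakest case in Table 1 is right about 65% of the time, where tossing a coin gives 50%, so noise that can be removed without recruiting anyone is worth removing. What is at stake is how often the pilot carries the better notification setting into the larger study.

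**Working it through.** **1. Reproducing Table 1.** Inputs from the article: the three pairs of rates, first look at 10, maximum 50, threshold 1% (taken as 0.01 absolute). Assumed: one yes/no response per person, 1:1 allocation, Beta(1,1) priors, updating after each pair. Simulating the unadjusted rule (4,000 runs per scenario) gives:

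| Rates | Stated | Simulated |
|---|---|---|
| 20% v 40% | 90% | 91.6% |
| 20% v 30% | 75% | 76.0% |
| 20% v 15% | 65% | 66.0% |

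A maximum of 100 gives 96%, 84% and 70%, which does not fit, so 50 covers both options together. The mean total at decision is about 24 to 31 people.

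**2. How much of the noise is habit.** With 25 per option and 20% completion, the variance of the raw difference is 2 × 0.16/25 = 0.0128 (SD 11.3 points). The habit part is ICC × 0.0128:

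- ICC 0.2: √0.00256 = 5.1 points
- ICC 0.3: √0.00384 = 6.2 points
- ICC 0.5: √0.0064 = 8.0 points

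These are as large as the 5-point effect. But the rest of the variance is (1 − ICC) × 0.0128, so the total stays at 0.0128 whatever the ICC. With one response per person, habit imbalance is a component of the binomial noise already in Table 1 and adds nothing to it.

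**3. What the history can remove.** With K earlier surveys, the approximate variance ratio after adjustment is 1 − ICC × [K·ICC / (1 + (K − 1)·ICC)].

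| ICC | K = 4, formula | K = 8, formula | Simulated (K = 4 / 8) |
|---|---|---|---|
| 0.2 | 0.90 | 0.87 | 0.91 / 0.88 |
| 0.3 | 0.81 | 0.77 | 0.83 / 0.79 |
| 0.5 | 0.60 | 0.56 | 0.62 / 0.58 |

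Fifty people then act like 50/0.91 = 55 to 50/0.58 = 86. At two or more survey requests a week, 4 to 8 earlier surveys means at most 2 to 4 weeks of participation.

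**4. Probability of a correct choice, fixed 25 v 25, one response each.** For 20% v 15% the SD is √((0.16 + 0.1275)/25) = 0.107, and Φ(0.05/0.107) = 68%. With a variance ratio of 0.83 this becomes Φ(0.467/√0.83) = 70%. Across the ICCs above, simulation gives 68% rising to 69–73%, and for 20% v 30%, 79% rising to 81–86%.

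**5. The same under the stated sequential rule.** Bayesian logistic fits, K = 4 or 8, one response each, 4,000 runs (Monte Carlo error about 0.7 points per figure):

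| ICC | 20% v 15%, unadjusted → adjusted | 20% v 30%, unadjusted → adjusted |
|---|---|---|
| 0.2 | 66.6% → 66.9–67.7% | 76.2% → 78.4–78.7% |
| 0.3 | 67.2% → 67.2–68.3% | 78.6% → 79.9–80.4% |
| 0.5 | 67.4% → 71.0% | 77.8% → 83.8–84.9% |

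The gain is about 0 to 3 points at ICC 0.2 to 0.3, hardly distinguishable from nil for 20% v 15%, and about 4 to 7 points at 0.5.

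**6. If several surveys per person count.** Fixed 25 v 25, 20% v 15%, with as many earlier surveys as outcome surveys. Six surveys each: 81.4% → 84.0% at ICC 0.12, 75.8% → 84.5% at 0.32, and 72.8% → 86.5% at 0.48, a gain of about 3 to 14 points.

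**The case against.** The strongest reply is that nothing here is wrong. The article names no model and excludes no covariate. Table 1 reproducing from two proportions shows how the design was simulated, not how the data will be analysed. Planning on unadjusted rates and adjusting later is ordinary practice, and covariates are often left to a fuller document. That stands: an unadjusted comparison is an inference, though a well-supported one, since the published rule and its operating characteristics both match it.

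The reply also has force on who is in the later evaluations. The article does not say whether each later group of 50 consists of re-allocated or new people. The target of 275 equals 5 × 50 × 1.1, which would also fit new people for each aspect, and these have no history. The allocation paragraph does state re-allocation after each evaluation, so some history will exist, but not necessarily for everyone.

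Two stronger readings are tempting. A reader might infer that habit imbalance biases the choice, or that Table 1 overstates the design's performance. Neither is supported: allocation is random, so the imbalance is chance error, and step 2 shows that with one response per person it is already counted. A reader might also take the fixed 25 v 25 gains as the expected benefit. The rule decides early, and under it the gains are smaller. Elsewhere the analysis plan says "We will analyse each MRPE after it has been delivered to 50 participants", which is closer to the fixed calculation, but the sequential rule is the one behind Table 1.

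Finally, a rich model is fragile at the first look. With 10 people at 20%, 2 responses are expected, and the chance of 0 or 1 is 0.8^10 + 10 × 0.2 × 0.8^9 = 38%. That stands, and it limits the remedy to a small model with stated priors.

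**Conclusion.** The point holds as a modest, inexpensive improvement in precision for evaluations 2 to 5. It is not a correction of Table 1, and no bias is shown. With one response per person under the sequential rule, the probability of choosing the better option rises by about 0 to 3 points at ICC 0.2 to 0.3 and by about 4 to 7 points at ICC 0.5. It is nil without stable habit and larger if several surveys per person enter the comparison.

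This rests on assumptions that the article does not settle: the ICC, 1:1 allocation, a history of 4 to 8 surveys, and that the people in the later evaluations have a history. The more of them who are new recruits, the smaller the gain.

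**What to change.** State whether completion before allocation enters the expected-loss calculation in evaluations 2 to 5, and whether those groups are re-allocated or newly recruited. If a fuller plan already covers this, one sentence is enough. If not:

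- In evaluations 2 to 5, compute the expected loss from a Bayesian logistic model with two main terms, option and the participant's completion rate before that allocation. Use weakly informative priors fixed in advance, add a no-history indicator for new recruits, and standardise the result back to the completion-rate scale so that the 1% threshold keeps its meaning.
- Keep the unadjusted rule for evaluation 1, where nobody has a history.
- Re-simulate Table 1 under the sequential rule for a stated range of ICCs, with the number of surveys per person made explicit.

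No extra participants, data collection or app changes are needed. The cost is the added simulation work and some dependence on the priors at the first look of 10, which the simulation should report.
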